An important part of the study is the involvement of the therapists. In order to improve adherence, the researchers will train the therapists before the inclusion of participants starts. The training will consist of the following parts (1) general background knowledge about attentional bias and ABM, (2) design and important parts of the study, and (3) the role of the therapists. During the training all therapists will receive a protocol in which all important aspects are described. In the first session of TAU after patients are assigned to the study, therapists will identify the time of the day patients’ craving is strongest and will instruct the patient to complete the ABM task at this particular time of the day. Furthermore, during each following treatment session of TAU, the therapist will ask the participant whether he/she trains on a regular basis, and will engage in motivational counselling if this is not the case.

During the last week of TAU in addiction care, participants in the training conditions will receive the last training invitation by e-mail. After completion, they will be invited for the post-assessment. Participants in the TAU-only condition will also receive the invitation for the post-assessment in their last week of TAU. Finally, 6 and 12 months after the end of TAU, all participants will receive an invitation for the follow-up measurements by e-mail. In case a participant does not respond to these invitations, the researcher will remind the patient via the preferred way (phone, e-mail, text message or app). Throughout the length of the whole project, a sounding board group will meet four times to monitor the process of the study. The group will include a researcher, a therapist, and a member of the client council of each addiction care centre, and an implementation professional.

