#### Questionnaires

Participants’ general health state is assessed by means of the EuroQol-5D-3 L questionnaire [49]. Health care-related costs are evaluated with the Treatment Inventory of Costs in Psychiatric Patients questionnaire [50]. The Measurements in Addiction for Triage and Evaluation questionnaire [51] is a standard instrument in the Dutch addiction care and will be completed during the intake and at the end of the treatment through the therapists. During the 6 and 12 month follow-up measurements, the same questions will be asked online. For this study, the following parts of the MATE will be evaluated: substance use, the Obsessive-Compulsive Drinking Scale (OCDS5), and the Depression Anxiety Stress Scale (DASS).

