#### Other measurements

During the baseline assessment, sociodemographic information will be collected, such as gender, relationship, level of education, and work. Furthermore, details of the patients’ own clinical history of addiction as well as of their family will be asked. Next, participants who are assigned to one of the training conditions will be asked about their expectations of the intervention. Before and after each training session, participants will rate their intensity of craving on a visual analogue scale (VAS), varying from 0 (no craving at all) to 100 (extreme craving). With this, possible direct effects of the intervention on subjective craving can be examined. Furthermore, at the end of the baseline assessment, all participants are asked to fill in a short questionnaire about their computer/laptop use in their private life. This information might be helpful when investigating for whom this iABM intervention was effective. Last, after the first week of training and during the post-assessment, participants, who are assigned to one of the training conditions, will be asked to fill in an evaluation questionnaire, in which they can give their opinion about the intervention and are asked to indicate whether the intervention helped them. Information derived from these questionnaires can be used as indications for possible next steps towards implementation. For an overview of all questionnaires and tasks per time point, see Table 2.

**Table 2 Tab2:** Overview of measurement instruments per time point

Purpose	Measures	Baseline	Post-assessment	Follow-up
Attentional bias assessment	Odd one out task	X	X	X
Baseline measures	Demographics	X		
	History of addiction	X		
	Family history of addiction	X		
Primary outcome measures - clinical	MATE (substance use, craving)	X	X	X
	Clinical state (relapse)			X
Primary outcome measures - Societal/economical	TiC-P	X	X	X
	EQ-5D	X	X	X
Secondary outcome measures	MATE (depression, anxiety and stress)	X	X	X
	Computer use	X		
Others	Expectation-questionnaire	X^a^		
	Training evaluation		X^a^	

^a^only to be filled in by participants in one of the training conditions

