### Sample size

To find a difference between groups of medium effect size with a power of 0.8 at an alpha of 0.05, both the treatment and the control arm need to include 64 patients, as calculated with.

G*power 3.1.5. Dropout rates in regular addiction treatment are known to be approximately 20%. Given the 6 and 12 months follow-up measurements a dropout rate of 40% was calculated. Therefore, a total amount of 213 patients will be recruited.

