### Withdrawal

All participants can withdraw from the study at any time. However, they are asked whether they are willing to complete the measurements. Thus, even if participants stop the training (iABM intervention), they are still invited to participate in the post-assessment and follow-up assessments.

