### Blinding

Since all assessments take place online, thus in the absence of the researchers, the outcome data are blinded. However, one researcher will be aware of the condition of the participants in order to support them appropriately when technical or personal problems appear. It is unlikely that this will entail problems of bias, as the researcher is not involved in any measurement and the motivational part of the study lies in the responsibility of the therapists. The therapists and participants will be blinded for the two training conditions. Therefore, the iABM intervention and the placebo condition were designed such that the use of the same task stimuli would be possible, making both conditions look very similar. Furthermore, it is unlikely that participants will tell their therapists much about the content of the training, but more about whether they train regularly or whether they like or dislike the training. This will help to keep the therapists blinded. Furthermore, the therapists will be instructed not to do any ‘research’ about what might be the ‘real’ intervention. Participants will be asked to indicate their expectation about their condition in the post-assessment.

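### The protocol contradicts itself on how the post-treatment MATE is collected, and states no way to obtain it from patients who leave TAU early

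*Protocol article*

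**What the plan says.** All references are to the protocol article.

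- **Source of the post MATE.** Under Questionnaires, the MATE "will be completed during the intake and at the end of the treatment through the therapists". The next sentence places the online version elsewhere: "During the 6 and 12 month follow-up measurements, the same questions will be asked online".
- **Mode of assessment.** Under Blinding: "Since all assessments take place online, thus in the absence of the researchers, the outcome data are blinded".
- **Role of the MATE.** Table 2 lists it at baseline, post-assessment and follow-up, for substance use and craving (primary) and for depression, anxiety and stress (secondary).
- **Trigger for the post-assessment.** Under Participants and procedure: "During the last week of TAU in addiction care, participants in the training conditions will receive the last training invitation by e-mail". The post-assessment invitation follows completion of that session. For the third condition: "Participants in the TAU-only condition will also receive the invitation for the post-assessment in their last week of TAU". The 6- and 12-month invitations are counted from the end of TAU.
- **Continued assessment.** The Withdrawal section says in general terms that participants who withdraw are asked whether they will complete the measurements. The one case it spells out is that "even if participants stop the training (iABM intervention), they are still invited to participate in the post-assessment and follow-up assessments".
- **Expected dropout.** Under Sample size: "Dropout rates in regular addiction treatment are known to be approximately 20"%. The sample size allows for 40% loss.
- **Analysis.** Under Clinical analysis, substance use and craving enter a repeated measures ANOVA over four time points, post included, with multiple imputation for missing data.

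**The concern.** The Questionnaires and Blinding sections cannot both be right about the post MATE. The Blinding section also rests its claim of blinded outcome data on the online mode, so the difference is more than wording.

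Under the Questionnaires section, both the source of the post MATE (the therapist, at the end of treatment) and its trigger (the last week of TAU) depend on the patient reaching a planned end of TAU. A patient who stops attending may have no closing session and no last week that is known in advance. The Withdrawal section invites such a patient to go on in general terms, but does not say who would administer the MATE, or when.

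The loss would not be random. Training runs until the end of TAU, so early leavers in the training conditions also receive less of it, and they may well differ in substance use. If their post values are systematically absent, the post-treatment comparison on two of the three primary clinical outcomes leans on TAU completers. The trial's hypothesis names post-measurement explicitly.

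**Working it through.** **1. The plan's own sample size.** Inputs from Sample size: medium effect (taken as d = 0.5), power 0.80, alpha 0.05 (taken as two-sided), 40% loss. The exact two-sample t-test gives 63.77, so 64 per arm and 128 in total. Then 128 / (1 − 0.40) = 213.3, which agrees with the stated 213.

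**2. Patients concerned.** Reading the 20% as dropout from TAU: 0.20 × 213 = 42.6, about 43. At 50/25/25 allocation that is about 21 iABM, 11 placebo and 11 TAU-only.

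**3. Power.** If only these patients lack a post value, 213 × 0.80 = 170.4 remain (85.2 per arm) and power for d = 0.5 is 0.90. At the planned 40% loss, 127.8 remain and power is 0.80. The number of patients is sufficient either way.

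**4. Possible bias at the post time point (illustration).** Assume d = 0.5 in TAU completers and 0 in early leavers.

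- Effect in all randomised patients: 0.8 × 0.5 + 0.2 × 0 = 0.40.
- If imputation gives leavers the completers' effect, the estimate is 0.50. The ratio is 0.50 / 0.40 = 1.25, a 25% overstatement.
- If leavers have the same effect as completers, the overstatement is 0.

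**5. The same case when follow-up MATE values are used.** Extend the assumptions to follow-up (effect 0.5 in completers, 0 in leavers), let leavers answer both online follow-ups, and let any two time points correlate at r. Regressing post on both follow-ups within arm gives each a coefficient of r/(1 + r). The imputed effect in leavers is then 0.5 × (1 − 2r/(1 + r)), and the pooled effect is 0.8 × 0.5 + 0.2 × that value.

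| r | Imputed effect in leavers | Pooled effect | Overstatement against 0.40 |
|---|---|---|---|
| 0.3 | 0.27 | 0.45 | about 13% |
| 0.5 | 0.17 | 0.43 | about 8% |
| 0.7 | 0.09 | 0.42 | about 4% |

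**6. Differential dropout (illustration).** Suppose TAU dropout differs by 10 points between arms (15% and 25%, assumed) and leavers are 0.25 to 1.0 SD worse. A completers-only contrast then shifts by 0.10 × 0.25 = 0.025 to 0.10 × 1.0 = 0.10 SD. With equal dropout and an equal deficit in both arms, the shift is 0.

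**7. The sections side by side.**

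| Question | Questionnaires | Blinding | Participants and procedure | Withdrawal |
|---|---|---|---|---|
| Mode of the post MATE | Through therapist | Online | Not specified for the MATE | Not stated |
| Timing | End of treatment | Not stated | Last week of TAU | Not stated |
| Patient who leaves TAU early | Not addressed | Not addressed | Not addressed | General request only; stopping TAU not named |

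**The case against.** A reader might infer that early leavers have no route at all to the post-treatment outcome, and that continued assessment covers only patients who stop the training. The document does not support either. The Withdrawal section's general sentence covers any withdrawing participant, and stopping the training follows from it as a consequence, not as its limit. The Blinding section, if correct, gives a route that needs no therapist.

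A reader might also take 25% as the expected overstatement. It is the top of an illustrative range. It requires no effect at all in leavers, and an imputation that ignores their follow-up MATE. The article says only that multiple imputation will be used, and the online follow-up MATE goes to all participants.

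The scope is limited too. Only the post time point is directly affected, relapse is assessed only at follow-up, and the sample size already allows for 40% loss.

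Finally, a condensed article may leave operational detail to the full protocol, and therapists receive a separate protocol. This is fair for how case closure is recorded. It does not dispose of the point, because the article does state a source and a trigger. Both depend on finishing TAU, and the source contradicts the Blinding section. The general request to withdrawing participants expresses an intention, not a mechanism, and a patient can leave TAU without withdrawing from the study.

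**Conclusion.** The contradiction between Questionnaires and Blinding is plain on the page and must be resolved. If the Questionnaires section describes what will happen, about 43 of 213 patients (at 20% TAU dropout) have no stated way of giving a post-treatment MATE, and the missing values would be concentrated in early TAU leavers.

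The resulting bias cannot be quantified from the document. Under the assumptions shown it lies between 0 and 25% of the true post-treatment effect, or about 4 to 13% when both follow-ups are answered and used with r between 0.3 and 0.7. The zero effect in leavers, the correlations and the differential dropout are assumptions. If the Blinding section is the correct one, the mode problem disappears, but the post-assessment date for early leavers is still undefined. So is the date from which their 6- and 12-month follow-ups are counted. The change is worth making because a missed post-treatment assessment cannot be collected later.

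**What to change.** 1. **Questionnaires:** ask the MATE questions already planned online for 6 and 12 months of all participants in the online post-assessment, and keep the therapist MATE as a supplementary source. This agrees with the Blinding section and gives post and follow-up the same mode. Sending the online questions only to patients without a therapist MATE would confound mode with TAU dropout, and a mode indicator could not separate the two. State the baseline mode as well, since the contradiction also covers intake.
2. **Participants and procedure:** define the post-assessment date, and the date from which 6 and 12 months are counted, for patients whose TAU ends early. Case closure or a fixed latest date after assignment would serve.
3. **Withdrawal:** name stopping TAU and stopping either training, in all three conditions, as cases in which assessments continue.

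The cost is a few extra online questions at post-assessment, an invitation trigger and a short amendment. The sample size does not change. If the baseline MATE stays with the therapist, mode changes between baseline and post, but in the same way in every condition.

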One strength of this study is the integration of a new developed multi-session iABM intervention with face-to-face TAU, given by a trained therapist. On the presumption that addiction is maintained by conscious as well as automatic processes, the combination of CBT-based intervention with its focus on strengthening decision-making processes and conscious reasoning and iABM intervention with its focus on modifying relatively automatic processes involved in addiction might well increase treatment outcome and reduce rates of relapse. We will embed the iABM intervention into TAU by asking the therapists to involve the iABM training in the regular treatment sessions. Therapists will motivate the patients to train regularly and according patients will experience that both interventions are connected and constitute one treatment program. A second strength of this study is that the iABM is a home-delivered internet-based intervention, thus allowing patients to train in the same environment where they tend to experience high levels of craving. As we have argued, the home of the patients diagnosed with substance use disorder might be the best context to deliver these trainings. Home delivery will give the patients more freedom and enables them to train when the experience of craving is strongest. Furthermore, home-delivered interventions are generally less expensive than those that require delivery in the clinic. This makes iABM interventions attractive, as they would be relatively inexpensive to implement, if proven effective. A third strength of the study is that it will investigate relapse rates and long-term effects with two follow-up assessments, at 6 and 12 months after the end of TAU and iABM intervention. Gladwin, Wiers and Wiers [53] have argued that follow-up measures may be essential to determine whether treatment innovations enhance outcomes in addictions, given that high relapse rates represents the major limitation of existing interventions. Because the effects of ABM interventions might be especially relevant in situations of stress or other negative circumstances in daily life, its benefits may become evident only across the month that follow treatment. A final strength of the study is that by gamifying the iABM intervention, we hope to improve upon prior approaches to ABM interventions. This more dynamic training mirrors the reality of engaging and disengaging of attention to a greater degree than previously used ABM intervention for substance use disorders. In addition, by adding game-like features to make the training more appealing, we expect that patients will be more inclined to train on a regular basis.

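### The end-of-treatment MATE is completed through therapists who know who is in TAU-only, so the statement that all outcome data are collected online and blinded does not hold at post

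*Protocol article*

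**What the plan says.** All passages are in the protocol article.

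- **Questionnaires:** the MATE "will be completed during the intake and at the end of the treatment through the therapists". Only the later measurements are described as online: "During the 6 and 12 month follow-up measurements, the same questions will be asked online". The parts used are substance use, the OCDS5 and the DASS.
- **Other measurements, Table 2:** MATE substance use and craving are primary clinical outcomes at baseline, post-assessment and follow-up. Relapse is listed at follow-up only.
- **Blinding:** "Since all assessments take place online, thus in the absence of the researchers, the outcome data are blinded". On the therapists: "The therapists and participants will be blinded for the two training conditions".
- **Participants and procedure:** the therapist tells the patient at what time of day to train, and "during each following treatment session of TAU, the therapist will ask the participant whether he/she trains on a regular basis", with motivational counselling if training has lapsed. Participants in all three conditions are invited to a post-assessment in the last week of TAU.
- **Discussion:** "Therapists will motivate the patients to train regularly".
- **Randomization:** 50% TAU + iABM, 25% TAU + placebo, 25% TAU-only.
- **Clinical analysis:** substance use and craving from the MATE are tested in a 4 (time) × 2 (iABM versus pooled controls) repeated measures ANOVA.

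**The concern.** Two statements about the same measurement conflict. One says that nothing is collected other than online. The other routes two primary outcomes at post through the treating therapist.

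The reason given for blinding also concerns the wrong person. That researchers are not present says nothing about a therapist who is. The Blinding section argues that the one unblinded researcher is harmless because that person takes no part in measurement and because motivation is the therapists' task. By the same reasoning the therapist is not harmless: he or she takes part in the post measurement and is responsible for the motivation.

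A patient whose therapist has encouraged the training for months may report less use or craving to that therapist than a TAU-only patient would. Such a shift would favour iABM over TAU-only, which Trial design names as the first of the two comparisons that the control conditions serve. It would also enter the pooled contrast used for the main hypothesis. A reader who relies on the Blinding section would take the post outcomes as protected when they are not.

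**Working it through.** **Step 1. Who knows what at post**

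| Contrast | Does the therapist know the difference? | Post MATE exposed? |
|---|---|---|
| iABM v TAU-only | Yes: one group trains, the other does not | Yes, in full |
| iABM v pooled controls | Yes, for the TAU-only half | Yes, in part |
| iABM v placebo | No, while blinding between the trainings holds | No |

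**Step 2. Which measurements are exposed.** The intake MATE precedes assignment, so it cannot depend on arm. The 6- and 12-month measures are online, and relapse is listed at follow-up only. That leaves one of the four ANOVA time points: post.

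**Step 3. Dilution.** Suppose the therapist route shifts post scores by *b* SD in both training conditions relative to TAU-only. TAU-only makes up 25/(25 + 25) = 0.5 of the controls. The shift is then:
- iABM v TAU-only: *b*
- iABM v pooled controls: *b* − 0.5*b* = *b*/2
- iABM v placebo: *b* − *b* = 0

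In the planned ANOVA only the post cell moves, by *b*/2. The group difference averaged over the four time points moves by (0 + *b*/2 + 0 + 0)/4 = *b*/8.

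**Step 4. The plan's own figure.** A two-sample t-test with d = 0.5 (taken as the medium effect), two-sided alpha 0.05 and power 0.80 needs 63.77, so 64 per arm, as stated in Sample size. With 40% dropout, 128/0.60 = 213.3, against 213 stated. The sample size reproduces and this point does not affect it.

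**Step 5. Illustration only.** The documents give no value for *b*, so a range is shown. The case is a comparison of post means alone, with no true effect and 64 analysed per arm:
- Pooled contrast: SE = √(2/64) = 0.177
- iABM (64) v TAU-only (32): SE = √(1/64 + 1/32) = 0.217
- Rejection rate = 1 − Φ(1.96 − shift/SE) + Φ(−1.96 − shift/SE)

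| Assumed *b* (SD) | Pooled shift *b*/2 | Rejection, pooled | Rejection, v TAU-only |
|---|---|---|---|
| 0.1 | 0.05 | 5.9% | 7.5% |
| 0.2 | 0.10 | 8.7% | 15.2% |
| 0.3 | 0.15 | 13.6% | 28.3% |
| 0.4 | 0.20 | 20.5% | 45.5% |
| 0.5 | 0.25 | 29.3% | 63.7% |

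The plan specifies no post-only test, so these are not error rates of the planned analysis.

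**The case against.** The strongest reply has four parts.

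- **The placebo arm deals with this.** Placebo patients meet the same therapists, the same questions about training and the same encouragement, and therapists are blinded between the trainings. This stands for iABM versus placebo. A reader might infer that a positive post result could never be told apart from therapist influence. The documents do not support that, because under the equal-shift assumption this contrast is not moved. It does not rescue the pooled analysis, which merges placebo with TAU-only.
- **The therapist may only pass on a form.** The wording does not say whether the therapist interviews and scores or just hands over a questionnaire, and that detail may sit in a fuller document. This stands: it cannot be claimed that therapists record answers more favourably. Influence on what patients report remains possible if the answers go to that therapist.
- **The differential may be small.** Therapists treat substance use in every arm, so pressure to report less use exists in TAU-only too. Only the increment from discussing the training differs, and counselling is given only when training lapses. This stands, and is why no size can be asserted.
- **The post MATE may in fact be online.** Table 2 lists it under the post-assessment, to which participants are invited. If so, the Questionnaires section is wrong and there is no exposure. That is a reason to correct the text, since both statements cannot be true.

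**Conclusion.** The point holds in a limited form. The article contradicts itself on how the post MATE is collected. If the Questionnaires section is right, post substance use, craving and DASS are unblinded with respect to TAU-only: in full for iABM versus TAU-only and at about half strength for the pooled contrast. The half rests on the 50/25/25 allocation and on an equal shift in the two training conditions.

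The size of any bias is unknown. A reader might take the table of rejection rates to mean that the trial's false-positive risk is, say, 9% or 20%. It does not show that: *b* is assumed, and the planned test uses four time points of which only post is exposed. Nor are the later follow-up results or relapse compromised by this route.

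The matter should be put right because primary outcomes are concerned and the correction is cheap, but it does not invalidate the trial.

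**What to change.** **Preferred change.** Reconcile Questionnaires with Blinding. Include the MATE substance-use, OCDS5 and DASS items in the online post-assessment that all three conditions already receive, using the online questions already planned for 6 and 12 months. Name that self-report as the post outcome. Keep the therapist-completed MATE as the routine care record and use it in a sensitivity analysis.

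**Cost.** Patients spend a little longer at post and answer some items twice. The mode of collection would change between intake and post, where it is now the same. That change is common to all arms, so it should not by itself create a difference between them. Some patients will not answer online, in a trial that already plans for 40% dropout; the therapist MATE gives a check on this. The change does not remove the patients' own knowledge that they are in TAU-only.

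**If the therapist MATE stays as the post outcome.** Remove the blanket blinding statement, state that the post outcomes are unblinded with respect to TAU-only, and report iABM versus placebo separately at post. This costs only text and one further reported contrast.
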